#### Sample size justification

The chosen sample size of 240 participants was informed by findings from a related economic incentive trial with caregivers of CALHIV [16]. This sample size will enable us to estimate retention of 85% (with *n* = 36 participants or less declining participation or lost to follow-up) to within a 5% margin of error with 95% confidence [16]. In our previous pilot trial, we recruited caregivers (regardless of COVID- 19 SRD grant status) over a 2-month period with a retention rate of 85% at follow-up [16]. This suggests that a sample size of *n* = 240 potentially eligible caregivers for this trial could be recruited and retained within timeframe. Moreover, 10 clusters per arm are within the trial budget.

### Data management

Data will be managed at the SAMRC project office according to the trial’s detailed data collection and quality assurance standard operating procedure. Survey data exports, audio files, and transcripts as well as costing workbooks will be stored in a password-protected project folder on the SAMRC electronic storage drive. The final electronic datasets, codebooks, Stata do files, and questionnaires will be stored on the SAMRC online microdata repository. Upon completion of the project, all data and devices will remain stored in a locked cupboard at the SAMRC-Durban main office, with hard copies of the study forms stored for up to 15 years.

### Statistical analysis

All statistical analysis will be performed using Stata V18.0 [38]. Baseline participant characteristics will be presented using descriptive statistics, including means, medians, and interquartile ranges. Feasibility outcomes will be analyzed using simple descriptive statistics (proportions) and results compared by arm. Linear mixed-effects models will be used for endline scores, adjusting for baseline scores and clustering. To account for the small number of clusters, the Satterthwaite correction will be applied to adjust the degrees of freedom in the linear mixed-effects models [39]. For all binary outcomes, depending on the prevalence of the outcome, we will use mixed effects logistic regression for prevalence less than or equal to 10% and log-binomial or robust Poisson regression when the outcome is common. The number of participants who completed baseline and endline interviews and attendance will be ascertained at each workshop to determine the retention rate.

For the economic evaluation, a breakdown of the total financial and economic costs for key cost categories will be presented to assess the feasibility of the trial, stratified by arm. The average cost per participant will be presented by the outcome. Costs will be presented in 2023 ZAR and USD and adjusted for inflation.

For the qualitative study, electronic audio files will be transcribed and verified by a study team member. A codebook will be developed and transcripts will be coded, with codes grouped into categories and, in turn, themes [40]. An intersectional analysis of the experiences of caregivers will be conducted by heeding stories of the ways intersecting identities shaped experiences during the pandemic [41]. Qualitative data will be used to illuminate preliminary patterns identified in the quantitative data and probe feasibility measures for the trial.

The team of investigators will be consulted to assess whether the hypothesized theory of change [27] was supported by the quantitative and qualitative data and to determine staff perceptions on project implementation; this will allow for the theory of change to be refined and strengthened and to assess the feasibility of the trial (see Table 1 for the study timeline).

**Table 1 Tab1:** Study timeline

	**Months 1–3**	**Months 4–6**	**Months 7–9**	**Months 10–12**	**Months 13–15**	**Months 16–18**	**Months 19–21**	**Months 22–24**

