### Setting and cluster eligibility

This study will be conducted in the largely peri-urban eThekwini Metropolitan Health District, in KwaZulu-Natal, South Africa. The eThekwini municipality includes a sampling frame of 35 government (public sector) HIV clinics within primary healthcare clinics, community healthcare centers, and outpatient hospital-based facilities. Approximately *N* = 20 HIV clinics (clusters) will be sampled. Clusters within a 25-km radius of the field office, providing antiretroviral therapy to *n* > 1000 patients, and previously involved in the CWeL or SSCF trials will be eligible to participate in this trial. Clusters who are already enrolled in an existing CRT mental health or gender-based violence (GBV) intervention will be ineligible for participation. Two clinics from nearby wards (geopolitical sub-divisions) will be selected and randomly assigned to the intervention or control arm.

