### Cluster randomization

Approximately 20 clusters will be recruited, with 12 participants per cluster and 10 clusters per arm resulting in 120 participants per arm. For each selected ward/s, the statistician will use a random number generator to assign one cluster to the intervention arm and one cluster to the control arm.

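### Common binary outcomes are given models with no stated allowance for clustering, and no binary model has a small-cluster correction, although the linear models have both

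*Protocol article*

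**What the plan says.** The Statistical analysis section of the protocol article treats three kinds of outcome differently within one paragraph.

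- **Scores.** "Linear mixed-effects models will be used for endline scores, adjusting for baseline scores and clustering". Because clusters are few, "the Satterthwaite correction will be applied to adjust the degrees of freedom in the linear mixed-effects models".
- **Binary outcomes with prevalence up to 10%.** "mixed effects logistic regression for prevalence less than or equal to 10" per cent. Clustering is modelled; no small-sample correction is named.
- **Common binary outcomes.** "log-binomial or robust Poisson regression when the outcome is common". No random effect, estimating-equation approach, cluster-robust variance or small-sample correction is named.

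The Cluster randomization section sets the scale: "12 participants per cluster and 10 clusters per arm resulting in 120 participants per arm". Under Setting and cluster eligibility, allocation is within local pairs: "Two clinics from nearby wards (geopolitical sub-divisions) will be selected and randomly assigned to the intervention or control arm". The article gives no ICC, and no significance level for binary outcomes.

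**The concern.** The unit of randomization is the clinic, and workshops are delivered to groups of caregivers from the sampled clinics, so outcomes within a clinic may be correlated. The article accepts this for scores and for rare binary outcomes, then drops the cluster term for common ones. A log-binomial model, or a Poisson model whose robust variance only repairs the Poisson variance assumption, treats 240 women as independent. With a positive ICC its standard errors are too small.

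A second gap concerns the number of clusters. With 20 clinics, a normal reference distribution is too optimistic even when clustering is modelled. The article acknowledges this and acts on it only for the linear models.

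The stakes are those of a pilot. An objective is to estimate effect sizes for a future trial. An interval that is too narrow on a binary measure, for example probable depression (CES-D-10 of 12 or more) if analysed as binary, would make the pilot look more informative than it is.

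**Working it through.** **The article's own precision figure.** The only one concerns retention: "This sample size will enable us to estimate retention of 85" per cent "to within a 5% margin of error with 95% confidence". The half-width is 1.96 × √(0.85 × 0.15 / n). This is 4.5 points at n = 240 and 4.9 points at n = 204 (240 − 36), so the figure reproduces. It contains no design effect, and it does not bear on the binary models beyond showing that the article supplies no ICC.

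**Inputs.** From the article: 20 clinics, m = 12 per clinic, 85% retention (12 × 0.85 = 10.2 per clinic at endline), and baseline numbers of 149 and 124 (Trial status). Assumed: ICC from 0 to 0.10 and prevalence 0.2, 0.3 or 0.5.

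**Analytic check, clustering ignored, clinics unpaired.** The design effect is DE = 1 + (m − 1) × ICC. The true error of a nominal 5% two-sided test is 2 × [1 − Φ(1.96/√DE)]. The interval has 1/√DE of its proper width.

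| ICC | DE | Analytic error | Interval width relative to correct |
|---|---|---|---|
| 0.01 | 1.11 | 6.3% | 0.95 |
| 0.02 | 1.22 | 7.6% | 0.91 |
| 0.05 | 1.55 | 11.5% | 0.80 |
| 0.10 | 2.10 | 17.6% | 0.69 |

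**Simulation under no effect.** Beta-binomial data, 20 unpaired clinics of 12, 40,000 replicates per setting. The Monte Carlo standard error is about 0.1 point near 5%: √(0.05 × 0.95 / 40,000). Ranges are over the three prevalences.

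| ICC | Individual-level variance, z | Cluster-robust, z | Cluster-robust, t on 18 df |
|---|---|---|---|
| 0 | 4.5% | 6.7% | 5.0–5.2% |
| 0.01 | 5.5–6.0% | 6.5–6.9% | 4.9–5.3% |
| 0.02 | 7.0–7.2% | 6.6–7.1% | 5.0–5.5% |
| 0.05 | 10.7–10.9% | 6.8–6.9% | 5.1–5.2% |
| 0.10 | 16.6–17.0% | 6.6–7.1% | 5.0–5.5% |

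Ignoring clustering with about 10 per clinic gives about 5.6%, 6.5%, 10% and 15% at ICC 0.01, 0.02, 0.05 and 0.10. With the baseline numbers of 149 and 124 it gives about 6%, 7.5%, 12% and 19%.

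**Effect of ward pairing** (ICC 0.05, prevalence 0.3). This lets part of the between-clinic variance be common to the two clinics of a pair.

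| Share common to the pair | Individual-level, z | Cluster-robust, z | Cluster-robust, t |
|---|---|---|---|
| 25% | 9.5% | 5.9% | 4.3% |
| 50% | 7.8% | 4.6% | 3.4% |
| 75% | 5.8% | 3.3% | 2.4% |

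Pairing reduces the excess. An analysis that respects clusters but ignores effective pairing becomes conservative.

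**Mixed logistic model** (1,000 replicates per setting; ICC 0.02, 0.05, 0.10). With z, error is 6.0–6.8% at prevalence 10% and 6.8–7.1% at 30%. With t on 18 df it is 3.9–4.7% and 5.3–5.6%. The Monte Carlo standard error here is about 0.75 point, √(0.06 × 0.94 / 1,000), so the excess on the rare-outcome branch is modest and less precisely established.

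**The case against.** The best defence is that silence is not a decision. The article never says that clustering will be ignored. Its binary sentence directly follows two sentences on clustering and few clusters, robust Poisson can mean cluster-robust, and a statistical analysis plan not shown here may give the variance estimator. This has force, and it rules out saying that the investigators have chosen to ignore clustering. It does not remove the point. The article goes beyond silence: it assigns models to all binary outcomes, specifies mixed effects in one branch and not the other, and attaches the small-cluster correction to the linear models by name. Log-binomial, the first-named option, carries no robust label to reinterpret. Even on the cluster-robust reading, a normal reference leaves about 6.5–7% with unpaired clinics.

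A reader might infer more than the document supports:

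- *That binary results will have error rates above 5%.* This depends on an ICC the article does not give, on the meaning of robust, and on pairing. At ICC 0 the no-cluster analysis gives about 4.5%. Nor is any 5% test stated for binary outcomes, so error rates here only stand in for interval coverage.
- *That the potential primary clinical outcomes are compromised.* Wellbeing, depressive symptoms and IPV are all defined as scores, which go to the corrected linear models. The CES-D-10 cut-off is given as a classification threshold; the stated outcome is change in score. Any experience of IPV is not a named outcome. The feasibility proportions are descriptive.
- *That switching between odds ratio and risk ratio at 10% prevalence is a flaw of the same order.* The threshold is fixed in advance and does not depend on the treatment contrast, and the two measures are close when the outcome is rare. Preferring one measure throughout is largely a matter of taste.

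**Conclusion.** The point holds in a conditional form. As written, the article names no allowance for clustering in the common-binary models and no small-cluster correction in any binary model, while providing both for scores. Taken literally, the intervals for common binary outcomes are too narrow whenever the ICC is positive and most of it is not shared within ward pairs.

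The size rests on assumed ICCs and prevalences. It runs from under one point of excess error at ICC 0.01 to about 12 points at 0.10 with unpaired clinics. It is much smaller if pairs share most of the between-clinic variance, and about 1.5 to 2 points if robust means cluster-robust with z and clinics are unpaired. The consequence is over-precise binary estimates for planning the full trial. It should be corrected, but it does not undermine the pilot's main results.

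**What to change.** Amend the binary-outcome sentence to state that:

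- common binary outcomes will be analysed by modified Poisson regression clustered on clinic (estimating equations or cluster-robust variance), with a small-sample-corrected variance and a t reference on cluster-based degrees of freedom, or by a clinic-level analysis of proportions;
- the mixed logistic model will also receive a small-cluster correction;
- the degrees of freedom follow the design: 20 − 2 = 18 if pairs are ignored, or about 20 − 10 − 1 = 9 if the analysis is stratified on the ten ward pairs.

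The 4.9–5.5% error above was obtained for the unpaired analysis on 18 df. The pair-stratified version was not simulated and should be checked before it is adopted.

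The cost is one sentence, a routine analysis and wider intervals. At ICC 0.05 with unpaired clinics, the interval is √1.55 × (2.101/1.96) = 1.33 times the width obtained by ignoring clustering. Compared with a cluster-robust interval using z, moving to t on 18 df adds about 7% (2.101/1.96 = 1.07). On 9 df the t multiplier is larger still, offset to the extent that pairing removes between-clinic variance.

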**Intervention co-development**								
Workshop planning	X							
Workshops (× 3)		X						
Pre-test of intervention		X						
**Pilot CRT**								
Recruitment, baseline interview, follow-up interview (staggered approach by cluster)			X	X	X	X	X	
Intervention Delivery								
Control Delivery			X	X	X	X	X	
**Qualitative study**								
Baseline and endline IDIs			X	X	X	X	X	
**Economic evaluation**								
Cost interviews at baseline and endline			X	X	X	X	X	
**Dissemination**								
Workshops (× 2)								X
Conference presentations								X

## Discussion

Several negative outcomes have been associated with informal caregiving of CALHIV, including depression, IPV, and financial insecurity. These negative outcomes compound with social inequities to impact both caregivers’ own wellbeing and their ability to provide care. Consequently, the aim of this study is to co-develop, test the feasibility, and assess the preliminary effectiveness and cost-effectiveness of a combined unconditional cash transfer and gender transformative economic empowerment intervention on the psychological wellbeing, gender equality, and economic outcomes of caregivers of CALHIV in KwaZulu-Natal, South Africa. The limited access to psycho-social support services and high unemployment during COVID- 19 have intensified the pressures placed on already burdened caregivers of CALHIV [42, 43]. Previous studies have identified the positive synergistic effect of supportive interventions on the relationship between informal caregivers and patients, improving the emotional and mental health of both parties [44]. Further, gender transformative interventions that support women have been found to reduce experiences of IPV and gender inequities by transforming underlying social systems and creating lasting change [19]. Consequently, by incorporating a gender-transformative component, this intervention may improve caregiver wellbeing by helping dismantle the social norms and systems that underlie the gender inequalities caregivers frequently experience. Additionally, economic livelihood strategies that economically empower individuals through improved access to resources have been found to improve livelihoods by increasing independence and social status and enabling women to exercise choice [15]. As such, this intervention has the capacity to provide caregivers with financial assistance that can contribute towards addressing their personal, caregiver, and household financial needs and concerns.

### Strengths

This study builds on previously conducted trials by incorporating themes such as gender equality and IPV, with the goal of evaluating the feasibility, effectiveness, cost-effectiveness, and acceptability of interventions aiming to improve the wellbeing and address the challenges of caregivers of CALHIV post-COVID- 19. In addition, this study employs a human-centered research design that centers the knowledge, experiences, and needs of community members through the co-development of intervention materials with an existing CAB, allowing power differentials inherent to the research-participant relationship to be addressed [45]. Further, the economic evaluation fills a notable knowledge gap regarding the cost-effectiveness of wellbeing-related interventions in South Africa. Finally, through the intervention co-development phase and incorporation of a CAB, this study acknowledges power dynamics inherent in the researcher-participant relationship to strengthen this participatory approach and facilitate the creation of a quality intervention that is sustainable, empowering, and builds capacity [46].

### Ethical considerations

Voluntary written informed consent will be obtained from participants prior to participation in the participant’s preferred language. Ethics approval for this trial has been granted from the SAMRC Human Research Ethics Committee (EC006 - 2/2023), the KwaZulu-Natal Department of Health (KZN DoH) (KZ_202304_010), and Simon Fraser University (30,001,806), a key collaborating institution. All participants will be reimbursed at least R150 for each physical interaction with the study team (i.e., baseline and follow-up surveys, workshops, and qualitative interviews). This amount will be for their time (i.e., R50), transportation (R50), lunch (R50), and carer costs (If applicable, will be treated on a case-by-case basis).

The trial is subject to the following ethical considerations. Notably, given the sensitive nature of certain questions or modules, there is the potential risk of participant discomfort or distress. To minimize this risk, female fieldworkers with a background in GBV research and HIV counseling have been hired. Additionally, fieldworkers have been trained to identify early signs of discomfort or distress, and counsel and link participants to appropriate care accordingly. Further, there is the potential to identify victims and perpetrators of abuse throughout the screening and workshop procedures. The study team will adhere to reporting requirements of the Children’s Act of 2005—Sect. 110 in the case of reported or suspected child abuse [47]. Additionally, a referral system will be implemented to ensure vulnerable groups or participants who have disclosed experiences of GBV or abuse are linked to local health care and social services that can adequately respond. Informed consent forms will highlight the procedures, with fieldworkers assuring participants that their confidentiality will be respected but managing expectations.

### Limitations

The trial is subject to the following limitations: (1) the sample is restricted to female caregivers accessing HIV clinics who are eligible for the COVID- 19 SRD grant, potentially limiting the generalizability of our findings. (2) There is the potential for social desirability bias to be present due to the sensitivity of the topics proved during the questionnaires and workshops. However, the trial attempts to minimize this bias by building rapport with participants throughout the process and prioritizing the creation of a safe space for participants to share their stories. (3) Participants have full autonomy on how they use the cash transfer each month meaning there is no guarantee that participants will utilize their cash transfer to improve their economic livelihoods through savings or other income-generating activities. (4) The sample size power calculation does not consider IPV despite it being a primary outcome. However, previous IPV studies have demonstrated that adequate time and sample are needed to be powered to make an impact on IPV [35, 48–50]. As such, findings from this trial will inform future studies that could address this limitation by implementing this intervention on a larger scale.

### Anticipated use of results

Ultimately, the results from this trial will contribute to our knowledge of the association between psychological wellbeing and gender inequities of caregivers in South Africa and potential strategies to enhance wellbeing and gender inequities. Further, this trial will improve our understanding of the challenges of implementing a long-term economic incentive to mitigate the negative impacts of caregiving in this context and potential factors that may impact the effectiveness of an intervention of this nature. Finally, this preliminary trial has the potential to inform a larger confirmatory trial which could be useful to policy makers when considering strategies to sustain the COVID- 19 SRD grant, post-pandemic recovery efforts, and social assistance programs for caregivers of CALHIV and others disproportionately burdened by compounding health and social crises.

### Trial status

Enrollment of clusters complete. Seven clusters have completed the intervention economic empowerment workshops, and three clusters are in progress. Baseline quantitative complete (intervention: *n* = 149, control: *n* = 124) and qualitative interviews (intervention: *n* = 10, control: *n* = 10 complete. Cash transfers are still ongoing, all clusters have received at least 1 payment.

## Data Availability

The data and materials from this trial are managed by the SAMRC online microdata repository and available on request. Access to the dataset will be limited to researchers whose research topic or analysis places are compatible, with consent and assent agreements from participants.

## Abbreviations

CAB: Caregiver Advisory Board
CALHIV: Children and adolescents living with HIV
CONSORT: Consolidated Standards for Reporting Trials
CRT: Cluster randomized trial
GBV: Gender-based violence
IDI: In-depth interviews
IPV: Intimate partner violence
KZN DoH: KwaZulu-Natal Department of Health
SAMRC: South African Medical Research Council
SMS: Short text messaging
SPIRIT: Standard Protocol Items Recommendations for Interventional Trials
SRD: Social Relief of Distress
SSCF: Stepping Stones and Creating Futures
